#### 2.4.3. Objectives 3, 4 and 5: Quantification of Serum Biomarkers of Bone Turnover and Inflammation

To assess the levels of bone turnover or inflammatory biomarkers in MM patients and patients receiving a negative myeloma diagnosis, fasting serum samples will be collected. Bone resorption and formation biomarkers (CTX-1 and P1NP, respectively) will be quantified by enzyme-linked immunosorbent assay. Serum inflammatory chemokines and cytokines will be quantified using a multiplex array system; measurements will include (but not be limited to) chemokine (C-C motif) ligand 3 (CCL3), epidermal growth factor (EGF), fibroblast growth factor (FGF-2), granulocyte colony-stimulating factor (G-CSF), Granulocyte-macrophage colony-stimulating factor (GM-CSF), interferon α2 and γ, interleukins 1α, 1β, 2, 3,4,5,6,7,8,9,10,13, 15, 18, platelet derived growth factor (PDGF), transforming growth factor (TGF)α, and tumor necrosis factor (TNF) α and β. Fasting serum samples from MM patients will also be collected following first-line treatment; changes in bone turnover and inflammatory biomarkers in MM patients upon completion of first-line treatment will be evaluated.

#### 2.4.4. Objectives 6, 7 and 8: Correlation Analyses

Data on bone innervation and serum bone turnover and inflammatory biomarkers in MM patients will be correlated to self-reported measures of pain, both at diagnosis and following first-line treatment.

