## Abstract

**Simple Summary:**

Multiple myeloma is a bone marrow cancer that often causes bone pain, but little is known about the pain characteristics and mechanisms in this condition. This clinical study aims to: 1. characterize the type, location and intensity of pain in myeloma patients, and its effect of quality of life, and 2. investigate whether the nerve fibers in the bone of myeloma patients are altered. We will also explore whether pain intensity is correlated to blood indicators of inflammation or bone damage. Study results will help identify the mechanisms of myeloma-induced bone pain, allowing the development of new analgesics for these patients.

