**Abstract:**

Multiple myeloma (MM) is a bone marrow neoplasia that causes bone pain in 70% patients. While preclinical models of MM have suggested that both nerve sprouting and nerve injury may be causative for the pain, there is a lack of clinical data. Thus, the primary aims of this clinical study are: (1) to provide a deep characterization of the subjective experience of pain and quality of life in MM patients; (2) to investigate disturbances in the bone innervation of MM patients. Secondary aims include exploring correlations between pain and serum inflammatory and bone turnover biomarkers. In a prospective, observational study (clinicaltrials.gov: NCT04273425), patients with suspected MM requiring a diagnostic iliac crest biopsy at Sheffield Teaching Hospital (UK) are invited to participate. Consenting patients answer seven standardized questionnaires assessing pain, quality of life and catastrophizing. Bone turnover biomarkers and inflammatory cytokines are measured in fasting serum samples, and bone innervation is evaluated in diagnostic biopsies. MM patients are invited to a follow-up upon completion of first line treatment. This will be the first deep characterization of pain in MM patients and its correlation with disturbances in bone innervation. Understanding how bone turnover and inflammation correlate to pain in MM is crucial to identify novel analgesic targets for this condition.

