MM is commonly considered a disease of the elderly, as age is an important risk factor for its development [11]. Importantly, it has been shown that QoL is one of the primary concerns in elderly cancer patients, who often find it more important to improve their QoL than their overall survival [12]. Therefore, incorporating measures of pain and QoL in studies assessing clinical interventions for the treatment of MM is of utmost importance. Pain in MM can be grossly classified as either bone pain, arising as a consequence of disease progression; chemotherapy-induced neuropathic pain, as a side effect of the main anti-myeloma medications commonly used to treat the disease, or procedural pain, derived from the invasive medical procedures conducted to treat the myeloma. However, despite the growing focus on pain management, knowledge on the characteristics and baseline presentation of pain and QoL in myeloma patients is scarce. Moreover, the underlying mechanisms of myeloma-induced bone pain are grossly understudied. In preclinical MM models displaying pain-related behaviors, both bone denervation [13] and nerve sprouting [14] of the bone marrow have been described; however, it remains unknown whether this reflects the clinical landscape. Therefore, clinical studies addressing changes in bone innervation in MM patients and their correlation to pain may shed some light on the mechanisms of myeloma-induced bone pain, and bone cancer pain in general.

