### 2.4. Study Procedures

#### 2.4.1. Objectives 1 and 5: In-Depth Characterization of Pain in MM Patients

Patients who consent to participate will receive a booklet with a total of seven standardized questionnaires (Table 1), which will provide a deep characterization of their subjective experience of pain. Data from myeloma patients at diagnosis will be compared with that of patients receiving a negative myeloma diagnosis (control group). MM patients will be asked to complete the same set of questionnaires upon completion of first-line treatment; data from MM patients at diagnosis and following first-line treatment will be compared. The questionnaires include:BPI (Brief Pain Inventory, short version): two-factor questionnaire assessing the severity and interference of pain [15,16]. The severity component assesses location and severity of the pain, as well the analgesic relief provided by current therapy, if any. The interference component is composed by an affective and an activity subdimension. The BPI includes a Visual Analogue Scale (VAS) for assessment of pain intensity, which will be used to establish correlations between pain and disturbances in bone innervation, serum inflammatory and serum bone turnover biomarkers. Data from this questionnaire will allow to draw comparisons between pain severity and interference between MM patients and controls.FACT–BP (Functional Assessment of Cancer Therapy–Bone Pain): Initially developed for the assessment of pain in bone metastases, it measures bone pain and its effect on quality of life. This will provide information on whether myeloma patients suffer from bone pain, compared to controls. Moreover, this questionnaire is sensitive to clinical changes following therapy [17], and will provide important information on whether first-line anti-myeloma treatment improves bone pain and its effect on quality of life in myeloma patients.PCS (Pain Catastrophizing Scale): assessment of the extent of catastrophizing, which is subdivided in three domains: rumination, magnification and helplessness [18]. Mounting evidence suggests that catastrophizing (i.e., enhancing negative, anxiety-inducing thoughts) plays an important role in the subjective experience of pain; to our knowledge, this will be the first data on the role of catastrophizing in myeloma-induced bone pain.EORTC QLQ-C30 (European Organization for the Research and Treatment of Cancer Quality of Life Questionnaire-Core 30): assessment of quality of life in cancer patients. This questionnaire contains a measure of global health status, functional scales (including physical, role, emotional, cognitive and social functioning) and symptoms scales (including fatigue, nausea/vomiting, pain, dyspnea, insomnia, appetite loss, constipation, diarrhea and financial difficulties) [19]. As this questionnaire is widely used to assess the effect of cancer on QoL, it will allow to contextualize the effect of myeloma on QoL in comparison to other cancer types.EORTC MY20 (European Organization for the Research and Treatment of Cancer Quality of Life Questionnaire-myeloma module 20): Supplementary module to administer alongside the EORTC QLQ-C30 for the assessment of disease symptoms, side effects of treatment, future perspective and impact of disease on body image perception [20]. This questionnaire will allow comparisons to other cohorts of myeloma patients.EORTC CIPN (European Organization for the Research and Treatment of Cancer Quality of Life Questionnaire-chemotherapy-induced peripheral neuropathy module): assessment CIPN through a sensory, a motor and an autonomic scale [21]. Administration of this questionnaire at diagnosis will provide baseline data to compare the follow-up data to, allowing the identification of CIPN development after treatment.painDETECT: identification of a possible neuropathic component of pain [22]. This questionnaire, in combination with the EORTC CIPN, will allow the distinction between myeloma-induced neuropathy and chemotherapy-induced peripheral neuropathy”.

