#### 2.4.2. Objectives 2 and 5: Immunohistological Characterization of Nerve Fibers Innervating the Bone Marrow in MM

Current guidelines for the diagnosis of MM require the presence of at least 10% clonal cells infiltrating the bone marrow [1]. Therefore, to effectively diagnose MM, the healthcare team routinely extracts diagnostic trephine bone biopsies of the iliac crest and process them for quantification of MM cell infiltration.

Upon finalizing the standard pathology procedures, the research team will access the bone biopsies (both diagnostic and following first-line treatment) and perform an immunohistological characterization of the existence, location and density of neuronal fibers. Bone biopsies from MM patients will be compared to those from patients with a negative myeloma diagnosis. Serial sections will be subjected to multiplex-immunostainings for the pan-neuronal marker PGP9.5 (protein gene product 9.5) combined with the sympathetic nerve fiber marker TH (tyrosine hydroxylase), allowing the distinction between sympathetic and non-sympathetic (presumably sensory) fibers, and the myelinated axon marker NF200 (neurofilament 200), allowing the distinction between myelinated and non-myelinated fibers. A similar protocol for nerve characterization in human bone biopsies has previously been optimized in-house [23]. The analysis will estimate the number of nerve profiles per marrow area (mm^2^) of all PGP9.5-positive nerve profiles and of the nerve fibers’ subtypes, their association with a nerve cluster [23] and the percentage of nerve profiles with another nerve profile within 25 µm. Moreover, the multiplex-immunostaining will be combined with markers for osteoclasts (tartrate-resistant acid phosphatase 5b, TRAcP5b), blood vessels (CD34/CD31) and myeloma cells (CD138), allowing the analysis of the neuronal fibers proximity to blood vessels, myeloma cells and osteoclasts. The analysis will estimate the percentage of nerve profiles with an osteoclast, blood vessel, myeloma cell and bone within 25 µm.

Following first-line treatment, it is standard of care to extract a new bone biopsy to evaluate the presence of malignant plasma cells and assess treatment efficacy. Follow-up biopsies from enrolled MM patients will be analyzed to address the differences in bone innervation at diagnosis and upon completion of first-line treatment. Analyses will be performed by a researcher blinded to patient’s disease diagnosis.

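### Pain is correlated with nerve and serum markers without a role for myeloma burden, yet the results are read as evidence on mechanisms and analgesic targets

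*Protocol article*

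**What the plan says.** Objectives 6 to 8 (Section 2.3) relate self-reported pain to innervation, to bone turnover markers and to cytokines, within myeloma patients, at two time points. Section 2.4.4 gives the method in one sentence: "Data on bone innervation and serum bone turnover and inflammatory biomarkers in MM patients will be correlated to self-reported measures of pain". Section 2.4.1 names the pain variable, the intensity scale of the Brief Pain Inventory, "which will be used to establish correlations between pain and disturbances in bone innervation, serum inflammatory and serum bone turnover biomarkers".

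Burden is measured. Section 2.4.2 says the care team takes diagnostic trephines and will "process them for quantification of MM cell infiltration". After treatment "it is standard of care to extract a new bone biopsy to evaluate the presence of malignant plasma cells and assess treatment efficacy". The research team's own myeloma-cell stain (CD138) has a spatial purpose, "allowing the analysis of the neuronal fibers proximity to blood vessels, myeloma cells and osteoclasts". Neither the infiltration figure nor the stain is mentioned in the correlation analyses, and the limitations subsection does not raise burden.

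On interpretation, the Simple Summary says "Study results will help identify the mechanisms of myeloma-induced bone pain" and the Abstract closes with "Understanding how bone turnover and inflammation correlate to pain in MM is crucial to identify novel analgesic targets for this condition".

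**The concern.** The article's own account makes burden a plausible common cause. The Introduction describes "bone pain, arising as a consequence of disease progression" and links myeloma bone disease to raised resorption; the Discussion reports tumor-induced nerve injury in a mouse model. A link from burden to cytokines is plausible but not stated. Restricting the analysis to myeloma patients removes the contrast with controls, but not the spread of burden among the patients.

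If burden drives both pain and a marker, the two will correlate even when the marker does nothing to pain. Section 2.4.3 lists 25 cytokines and growth factors besides CTX-1 and P1NP, so one shared cause could move many markers together and look like a coherent mechanism. At stake is whether a marker of tumor load is taken for a candidate analgesic target.

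**Working it through.** **Inputs from the article**
- Section 2.4.5: at least 35 participants, at least half with myeloma. 35 × 0.5 = 17.5, so about 17 to 18 patients for the correlations.
- Section 2.4.5: difference 2.75, SD 2.75, 80% power, 17 per group.

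**Assumed inputs**
- Correlation of burden with pain and of burden with the marker, taken as equal: 0.3 to 0.7.
- Two-sided 5% tests.
- Reliability of iliac-crest infiltration as a measure of true burden: 1 or 0.5.

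**The plan's own figure.** The standardised difference is 2.75 / 2.75 = 1. A two-sided 5% t-test at 80% power needs 16.7, rounded up to 17 per group; power at 17 is 80.7%. The figure reproduces, but it concerns the group comparison. No figure is given for the correlations.

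**Correlation produced by a common cause alone.** With no effect of marker on pain, r(marker, pain) = r(burden, pain) × r(burden, marker). For example, 0.6 × 0.6 = 0.36.

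**Chance of p < 0.05 for such a marker, n = 17.** Simulated normal data, Pearson and partial Pearson tests, 40,000 or more replicates per setting:

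| Each burden link | Induced r | Crude | Partial, burden measured without error | Partial, reliability 0.5 |
|---|---|---|---|---|
| 0.3 | 0.09 | 6% | 5% | 5% |
| 0.5 | 0.25 | 16% | 5% | 8% |
| 0.6 | 0.36 | 30% | 5% | 13% |
| 0.7 | 0.49 | 54% | 5% | about 24% |

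At a link of 0.4 the crude rate is 9%. With 18 patients the crude rates for 0.3, 0.5, 0.6 and 0.7 are 6%, 17%, 32% and 57%.

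**Cost of adjustment in degrees of freedom.** By Fisher's z, the correlation detectable at 80% power is tanh(2.80 / √(n − 3)) crude and tanh(2.80 / √(n − 4)) with one covariate. For n = 17: tanh(2.80 / √14) = 0.63 and tanh(2.80 / √13) = 0.65.

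**The opposite case: the marker is a true mediator.** Let burden act on pain only through the marker, with a marker–pain correlation of 0.6. The crude test has 76% power at n = 17. The partial correlation is (0.6 − 0.6b²) / √[(1 − 0.36b²)(1 − b²)], where b is the burden–marker correlation:

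| b | Partial r | Power of partial test |
|---|---|---|
| 0.6 | 0.51 | 56% |
| 0.7 | 0.47 | 48% |
| 0.8 | 0.41 | 36% |

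A genuine mediator would therefore miss significance after adjustment in 44% to 64% of studies, against 24% before it.

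**The case against.** **Silence.** Section 2.4.4 is one sentence. It does not say that the correlations are unadjusted, and covariates are the kind of detail that a condensed article leaves to a full protocol or analysis plan. This stands against any claim that adjustment has been ruled out. It does not remove the point, which rests on two things the article does state: a plain correlation as the analysis, and mechanisms and targets as what it is meant to inform.

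**Exploratory framing.** The Abstract lists the serum correlations under secondary aims and speaks of exploring them. The mechanism sentence in the Simple Summary covers the whole study, including the comparison of innervation with controls. A reader might infer that the plan will declare any significant marker a drug target. No such decision rule exists; the target sentence is motivation. A purely descriptive correlation needs no adjustment, so the point bites only where the interpretation goes further.

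**Measurement of burden.** A reader might infer that infiltration is quantified in every biopsy. Section 2.4.2 supports this at diagnosis only; at follow-up it speaks of evaluating the presence of malignant cells, so a percentage may not exist. Iliac-crest infiltration is also a local measure, and the limitations subsection concedes that disease and pain may lie elsewhere. This stands, and it limits what adjustment can do.

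**Mediation.** The Discussion's hypothesis is a chain from tumor to nerve injury to pain. Adjusting for the start of a chain weakens the test of its middle link, as the second calculation shows. This stands, and it rules out treating the adjusted p-value as a verdict on a marker.

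**Conclusion.** The point holds as a mismatch between the stated analysis and the stated interpretation. A crude correlation among about 17 patients cannot tell a pain mechanism from a marker of burden. If burden correlates 0.5 to 0.7 with both pain and an inert marker, that marker reaches significance in 16% to 54% of studies instead of 5%; if the links are near 0.3, the inflation is negligible. The article gives no link strengths, so the size rests entirely on that assumption.

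Two stronger readings are tempting. One is that adjustment removes the problem: it does so only with error-free measurement of burden, and otherwise only in part. The other is that whatever fades after adjustment is merely a burden marker: the mediation result shows why that does not follow. Nor do the documents support saying that every marker will be affected after treatment.

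**What to change.** In Section 2.4.4:

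1. Beside each crude correlation with pain, report the partial rank correlation given percent plasma-cell infiltration, both with confidence intervals. Do this at diagnosis, and at follow-up wherever a percentage is recorded.
2. Label both sets exploratory.
3. State that a crude correlation alone does not separate a pain mechanism from a marker of disease burden.
4. State that loss of significance after adjustment will not be used to classify a variable as a burden marker only.

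The cost at diagnosis is wording and analysis, since infiltration is already quantified there. At follow-up a percentage may have to be recorded. Each adjusted correlation loses one degree of freedom, and more power where marker and burden are closely related. Some confounding will remain because iliac-crest infiltration is a local measure.

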#### 2.4.5. Sample Size Calculation

Power calculations for this study have been performed in relation to pain intensity scores between firstly diagnosed, untreated, MM patients and patients receiving a negative myeloma diagnosis (control group). The power calculation has been performed on the primary aim: pain in multiple myeloma, as measured in the numeric rating scale contained in the BPI, in which worse pain is scored in the 11-point numeric scale (0 = no pain, 10 = worst imaginable pain). Power calculations were performed using a pain intensity difference and a standard deviation of 2.75 in the 11-point numeric scale, as previously reported for MM patients [24]. For a power of 80%, our study requires a sample size of 17 patients per group.

The recruitment phase of this study will take place from October 2019 to June 2021. Based on historical experience, it is expected that 50 eligible study candidates will be identified and at least 35 are expected to participate, as the study involves minimal invasive procedures. We expect that at least half of the enrolled patients will be diagnosed with multiple myeloma, and data from patients with a negative myeloma diagnosis (MGUS or SMM patients) will be used as control.

## 3. Discussion

Pain is one of the most prevalent and feared cancer symptoms, and, together with fatigue, the main complain of MM patients [4,7]. The aim of this study is to provide a deep characterization of the subjective experience of pain, as perceived by MM patients, at time of diagnosis. Moreover, we will analyze the effect of first-line treatment on both pain and QoL.

Over the last few decades, methods to monitor symptoms and adverse effects, which ultimately contribute to the patients’ QoL, have gained attention. Traditionally, adverse effects are monitored by the clinicians following the Common Terminology Criteria for Adverse Events guidelines [25]. However, recent studies have shown that patient-reported outcomes (PRO) may be more accurate measures of patients´ symptoms, as clinicians often underestimate adverse effects [26]. This is also true in MM, as highlighted by a recent Danish study in which a poor correlation between PRO and clinician-reported adverse effects was found for all evaluated symptoms, including peripheral neuropathy, diarrhea, nausea and vomiting, fatigue, insomnia and appetite loss [27]. To overcome this, our study will apply a constellation of widely used, validated PROs to characterize myeloma-induced bone pain. These questionnaires include the short version of the BPI, which is the most commonly used tool for the evaluation of cancer pain [28] and assesses least, worst and average pain through numeric rating scales, which have been proved to have more power to detect differences in pain intensity than verbal categorical rating scales [29]. Additionally, the BPI evaluates the affective component of pain by assessing the relations with others, life enjoyment and mood, and the interference of pain with daily life, including walking, general activity and work. In combination with the FACT-BP, specifically developed for the assessment of bone pain, and the PCS, which focuses on catastrophizing and fear of pain, we expect to be able to capture relevant information on all pain dimensions (sensory, cognitive and affective) in myeloma patients.

To correlate the pain results to QoL, recruited patients will fill out the EORTC QLQ-C30 and EORTC QLQ-MY20, which are commonly used questionnaires for the evaluation of QoL in cancer and myeloma patients, respectively. As both these questionnaires have commonly been used in clinical studies with MM patients, they will allow comparisons to the published data regarding QoL in other patient cohorts [30,31,32].

Due to the preclinical evidence of nerve disturbances in the bones of myeloma-bearing mice presenting pain-like behaviors [13,14], we suspect that bone pain in myeloma patients may have a neuropathic component, even before receiving medication that may cause neuropathy (e.g., chemotherapy, proteasome inhibitors). For that reason, the EORTC QLQ-CIPN20 and painDETECT questionnaires will be administered, in an attempt to identify whether the pain of non-chemotherapy-treated myeloma patients (baseline measurements) presents a neuropathic component. We expect that the combination of these validated, standardized questionnaires will provide a deep characterization of pain in this patient population, allowing comparisons with other well-characterized populations such as patients with metastatic bone disease.

A common limitation of PRO to monitor HRQoL in longitudinal studies is the lack of compliance, which can compromise the power of clinical studies [33] and cofound the results (i.e., if the frailest patients do not complete PROs and drop out, the study results may overestimate QoL and underestimate toxicity and symptom burden). Recently, a Danish multicenter study evaluated, for the first time, a range of strategies to increase compliance to PRO in a population of myeloma patients [34]. In this study, myeloma patients at all disease stages were invited to participate by filling in PROs at 12 months intervals during a total of 24 months; the only exclusion criteria were set up as patients who do not speak Danish, or patients with a diagnosed psychiatric condition, so that the “real population” of myeloma patients in Denmark was represented. The results of this study showed that real-time monitoring of non-response patients, sending electronic reminders and educating study nurses leads to an increase of up to 95% PRO response rate, with frailty being a strong predictor for non-completion of self-administered questionnaires [34]. In an effort to improve compliance, patients recruited for this study will be given the option to fill in the questionnaire booklet themselves (self-reported PRO) while waiting for procedures in the hospital or take them home and return them in their next appointed visit. Follow-up calls will be placed to patients who fail to return the questionnaires within the agreed time-period. Thus, we expect compliance in this study to be high.

In the clinic, diagnosis of MM requires the immunohistological characterization of clonal plasma cells in the bone marrow. In this study, we will access diagnostic iliac crest biopsies. Sensory and sympathetic nerve profiles will be evaluated in serial sections, allowing the study of correlations between disturbances in bone innervation and pain parameters. We have previously observed tumor-induced nerve injury in a mouse model of myeloma-induced bone pain, which we hypothesize may be causative for the pain [13], while nerve sprouting has also been described in animal models of myeloma [14]. However, due to the lack of human studies on bone innervation in myeloma patients, it is unknown whether this translates to the clinical situation. Previous studies of bone innervation in primary hyperparathyroidism patients revealed that the majority of nerve profiles are closely associated with blood vessels, and that the density of nerve profiles innervating the bone marrow is higher above bone remodeling surfaces [23]. Moreover, histological studies of the bones of MM patients have shown that myeloma cells often disrupt the canopies covering bone remodeling compartments, leading to the fusion of myeloma cells with osteoclasts to create osteoclast hybrid cells [35]. To the best of our knowledge, no study has characterized nerve fibers in the bone of MM patients. Thus, immunohistological characterization of osteoclasts and clonal plasma cells in relation to nerve fibers and blood vessels in these patients will contribute towards elucidating the peripheral mechanisms of myeloma-induced bone pain.

As MM is characterized by the uncoupling of bone resorption and formation and the consequent development of osteolytic bone lesions, we will quantify bone turnover through analyzing the systemic levels of CTX-1 and P1NP. Presently, it remains unclear whether osteolytic lesion development is a direct driver of bone pain, as bisphosphonate treatment has shown dramatic effects on bone remodeling but their analgesic effect on bone cancer remains controversial [36]. To our knowledge, this study will be the first to evaluate correlations between bone resorption biomarkers and pain in MM. Additionally, we will investigate correlations between circulating cytokine levels and pain. It has previously been shown that interleukin-6 is positively correlated with pain intensity in advanced, stable multiple myeloma [37] and several other inflammatory cytokines that have been correlated to pain in patients with cancer-induced bone pain [38,39]. This will be the first study to investigate correlations between circulating cytokines and pain in firstly-diagnosed myeloma patients.

